#### **6.1.8 Manufacturer's Product Information/Investigators Brochure (IB)**

The manufacturer's Product Information for sulfasalazine (traded as Salazopyrin EN) is given in *Appendix 1*.

### **6.2 DOSING REGIME**

Trial subjects will receive a daily total of 3 grams of sulfasalazine, divided into 2 equal doses of 1.5 grams each, to be administered post-breakfast and post-dinner. Salazopyrin EN tablets should be taken whole, following a meal, as per the manufacturer's guidelines. The doses should be as evenly spaced as possible.

### **6.3 DOSAGE CHANGES**

In the event that a participant experiences mild to moderate gastrointestinal side effects from taking sulfasalazine, but still wishes to participate in the trial, the dosage regime would be titrated down to a total of 2 grams per day in an attempt to mitigate the severity of the symptoms. If these symptoms resolve, the Site Leader may titrate the participant's dose back up to 3 grams daily according to their clinical judgement. Any participants who experience severe side effects associated with sulfasalazine therapy will be withdrawn from the study and revert to standard clinical management of preeclampsia. See *Section 10.4.4* for definitions of event severity.

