Participants will be visited every 1-3 days from recruitment until delivery (while they remain inpatients) by a member of the research team to monitor for AEs or possible side effects of sulfasalazine, and to ensure the participant's ongoing willingness to participate in the trial. Participants who are discharged home prior to the birth of their baby will be reviewed by a researcher each time they attend their hospital for an outpatient review until they are readmitted or their baby is born. A member of the research team will be on call to attend or for advice relating to concerns raised by the participants or the clinicians providing their direct care.

Biochemical markers of preeclampsia disease (such as LFTs and proteinuria) will be monitored as a part of standard clinical care. The researchers will also have access to these routine pathology results – this data forms some of the secondary outcomes of the study.

The timing of delivery and any deviations from routine clinical care will be determined by the treating clinician or obstetric unit – not by a member of the research team. In the case where a member of the research team is also acting as the treating clinician, these decisions will be made in consultation with other members of the treating obstetric unit, with the best interests of mother and baby as the paramount consideration.

The medical histories of babies born to participants (including any pathology results from tests ordered by the treating clinicians) will be reviewed postnatally to assess for neonatal outcomes and AEs. A 'closing out' visit on the postnatal ward (or phone call following maternal discharge) will be made following the delivery of each participant's baby.

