## **5.6 WITHDRAWAL OF STUDY PARTICIPANTS**

Participation in the study is completely voluntary. Participants will be made aware of their ongoing right to discontinue taking sulfasalazine or to withdraw entirely from the study at any time, and for any reason. The research team also retains the right to discontinue a participant from taking sulfasalazine and initiating their withdrawal from the study at any time, if it is deemed by a Principal Investigator or Site Leader to be in the patient's and/or her baby's best interest(s).

If a participant is withdrawn from the study by a researcher due to a *Serious Adverse Event* (SAE), the relevant hospital Site Leader will arrange for medical follow-up visits or other contact with the treating hospital until the event has been resolved or stabilised. Any data collected from the participant up until their removal from the study will still be used in statistical analyses, unless this is specifically refused by the participant.

If a participant withdraws their consent to the study at any point, no further data will be collected about them by the research team. However, permission will be sought to continue using anonymised data and research samples collected from the participant up until the point of withdrawal. The research team will attempt to identify with the participant the reason/s for their withdrawal, in case a study protocol amendment and/or medical follow-up visits are warranted.

The research team will make reasonable attempts (i.e. attempting to make contact on  $\geq 3$  occasions, using more than one mode of communication) to locate a participant before they are deemed to be 'lost to follow-up'. If a participant is deemed to be lost to follow-up, but has not indicated to the research team that they wish to be withdrawn from the study, their anonymised data and any collected samples will still be used in the final analysis.

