#### 6.5 OVERDOSE

According to the Manufacturer's information (*Appendix 1*), sulfasalazine has a low per oral toxicity, except in the case of a hypersensitivity reaction. Similar to other sulphonamide drugs, the common signs and symptoms of a hypersensitivity reaction to sulfasalazine include gastrointestinal symptoms (nausea, vomiting and diarrhoea), haematuria, crystaluria or anuria. Central nervous system symptoms such as dizziness or convulsions may occur in more advanced cases, although it is not anticipated that participants will be on a high enough dose of sulfasalazine for long enough for these advanced symptoms to develop in relation to the medication (see *Appendix 1*). There is no specific

antidote for sulfasalazine overdose – any reactions should be treated symptomatically and supportively. Withdrawal of a participant from the trial following a sensitivity reaction will be considered and discussed between the research team, the participant and the participant's treating obstetric unit, and will depend on the nature and severity of the reaction. The *Victorian Poisons Information Centre* can be contacted any time on [name] for advice in the event of a suspected overdose.

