#### 10.4.4 Assessment of severity

The assessing Investigator will assign one of the three following categories of severity for each AE/SAE, and record their findings on the CRF/AE form:

- ‘Mild’: An AE that is easily tolerated by the participant, causing minimal discomfort and does not interfere with normal, daily activities
- ‘Moderate’: An AE that causes sufficient discomfort and interferes with the participant’s normal, daily activities
- ‘Severe’: An AE that prevents the participants from being able to perform their normal daily activities

Note: ‘Severity’ and ‘seriousness’ should not be confused – a severity rating is used to describe the intensity of an event, while seriousness is a regulatory definition based on participant or event outcome (see *Section 10.1*). One AE might be serious but not severe (e.g. thrombocytopenia), while another could be severe but not serious (e.g. nausea).

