## **10.7 FOLLOW UP PROCEDURES**

After recording an AE on the CRF (or recording and reporting a SAE), the event will be followed by the research team until a final outcome can be recorded. This may include follow up visits, assessments or other contact with the affected participant that are supplementary to the course of normal clinical care.

If a resolution to an event cannot be established by the Investigators, an explanation of the efforts made to do so will be recorded in the CRF or AE log; or as an addition to the SAE reporting form submitted to HREC and the PIs.

Follow-up information from any SAEs will be reported as updates to the initial report form and submitted by the PIs within regulatory timeframes to the TGA and/or the local HREC (as appropriate).

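### Section 6.3 takes women with severe side effects out of the study, not just off the drug, and nothing secures their delivery and neonatal outcomes, which are primary safety data

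*Protocol*

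**What the plan says.** Section 6.3 offers dose reduction to 2 g per day for mild to moderate gastrointestinal effects. For severe effects the rule is mandatory: participants with "severe side effects associated with sulfasalazine therapy will be withdrawn from the study and revert to standard clinical management of preeclampsia". Section 10.4.4 defines severe as preventing normal daily activities and separates this from seriousness, giving nausea as an effect that can be severe without being serious.

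Section 5.6 gives the participant two distinct choices: to stop the drug, or to leave the study altogether. For a stop made by the team it joins the two, reserving the right to "discontinue a participant from taking sulfasalazine and initiating their withdrawal from the study at any time". When a researcher withdraws a woman because of an SAE, section 5.6 provides "medical follow-up visits or other contact with the treating hospital until the event has been resolved or stabilised", and adds: "Any data collected from the participant up until their removal from the study will still be used in statistical analyses" (unless she refuses). Its rule that no further data are collected is tied to withdrawal of consent.

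Four other provisions bear on the point:
- Section 10.7: after an AE is recorded, "the event will be followed by the research team until a final outcome can be recorded".
- Section 3: the histories of participants' babies "will be reviewed postnatally to assess for neonatal outcomes and AEs", with a close-out contact after delivery.
- Section 10.2: AEs and SAEs are recorded from consent to the postnatal close-out.
- Section 8: data are collected, where possible, whatever the compliance with treatment.

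**The concern.** The main purpose of the trial is safety, and section 2.1.1 lists fetal and neonatal mortality and morbidity among the primary safety data. Most of that information arises at or after birth. A woman removed under section 6.3 leaves before then.

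Removal is triggered by toxicity. If her later outcomes are not collected, the loss is not random: the babies missing from the safety summary are those whose mothers reacted worst to the drug. No analysis can recover outcomes that were never collected. The trigger is also not confined to rare events, because severity is defined by interference with daily activities and section 10.2 describes gastrointestinal effects as known and common. With 20 women and no comparison arm, each baby is worth 5 percentage points of a reported rate (1/20).

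**Working it through.** The plan states no figure on this point, so there is none to reproduce. The check has two parts: what the text secures, and how much could be at stake.

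**1. What is secured after a team-initiated removal**

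- *Removed for a serious event.* Section 5.6 follows the event until it resolves or stabilises and retains data collected up to removal. Neither provision reaches the birth.
- *Removed for a severe but non-serious event.* The SAE paragraph of section 5.6 does not apply. Section 10.2 requires a severe gastrointestinal effect to be recorded as an AE, so section 10.7 follows that event to its outcome. It does not extend to delivery or the neonate.
- *Sensitivity reaction.* Under section 6.5, "Withdrawal of a participant from the trial following a sensitivity reaction will be considered and discussed between the research team", the participant and her treating unit. This leaves removal to discretion and says nothing about later data.
- *General provisions.* Sections 3 and 10.2 are written for participants. Section 8 concerns compliance and is qualified by feasibility. None says whether it still applies to a woman withdrawn from the study.
- *Prohibition.* There is none. The bar on further data in section 5.6 covers withdrawn consent, and section 5.4 covers women who are ineligible, decline or withdraw consent.

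Delivery and neonatal outcomes after removal by the team are therefore unsecured, though not excluded.

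**2. Possible size**

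Inputs: n = 20, single arm (sections 3 and 9.1). Assumptions, because the protocol gives no rates: k women removed with outcomes not collected, k = 1 to 4, and 4 neonatal events among the 20 − k who stay.

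- Reported rate = 4/(20 − k).
- Lowest rate among all dosed women (no removed woman's baby has an event) = 4/20.
- Highest rate (every removed woman's baby has an event) = (4 + k)/20.

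Intervals are two-sided 95% Clopper–Pearson.

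| k | Reported | Lowest among all 20 | Highest among all 20 |
|---|---|---|---|
| 1 | 4/19 = 21.1% (6.1–45.6) | 4/20 = 20% (5.7–43.7) | 5/20 = 25% (8.7–49.1) |
| 2 | 4/18 = 22.2% (6.4–47.6) | 4/20 = 20% (5.7–43.7) | 6/20 = 30% (11.9–54.3) |
| 3 | 4/17 = 23.5% (6.8–49.9) | 4/20 = 20% (5.7–43.7) | 7/20 = 35% (15.4–59.2) |
| 4 | 4/16 = 25.0% (7.3–52.4) | 4/20 = 20% (5.7–43.7) | 8/20 = 40% (19.1–63.9) |

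The chance that the rule is used at all is 1 − (1 − p)^20, where p is the assumed probability of a severe side effect. For p = 5%, 10%, 15% and 20% this gives 64%, 88%, 96% and 99%.

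The reduced denominator alone costs little. With no events, the two-sided 95% upper limit moves from 16.8% (0/20) to 18.5% (0/18) or 20.6% (0/16). What matters is that the missing outcomes would be selected by toxicity.

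**The case against.** The strongest reply is that the protocol never tells anyone to stop collecting. The no-further-data rule belongs to withdrawn consent, and the sentence on data up to removal says those data are used, not that only those are. Sections 3, 8 and 10.2 set general defaults with no exception for removal by the team, and a default need not be restated for every subgroup. Actual loss is also unlikely: women start as inpatients at two hospitals, most are expected to stay until delivery (section 6.1.7), and neonatal outcomes come from medical records that exist whether or not the mother is on the drug. The numbers removed and the event count are assumptions, the upper bounds need every removed woman's baby to have an event, and a descriptive trial has no decision threshold to cross. Section 1.3 also expects dose-related effects mainly above 4 g per day, against 3 g here.

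Much of this stands. There is no prohibition, the records will probably exist, and the sizes are illustrative. It does not remove the problem. Section 6.3 is a mandatory instruction to withdraw from the study, and section 5.6 shows that the protocol distinguishes this from stopping the drug. A site could reasonably read a withdrawn woman as no longer a participant, in which case the defaults in sections 3 and 10.2 no longer reach her. Two sites could read it differently.

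**Conclusion.** The concern holds. Section 6.3 ends study participation where ending dosing would do, and no section expressly secures delivery and neonatal outcomes for a woman removed by the team. It is an unsecured outcome and a tension between sections, not a ban on collection.

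Under the assumption of 2 removals and 4 observed events, a reported 22% would stand for a rate among all dosed women of 20% to 30%. With 1 removal the range is 20–25%, and with 4 it is 20–40%. These figures rest on assumed removals and events and on the removed women's outcomes not being collected. If no one is removed, or their records are reviewed anyway, the effect is nil. The change should be made because any loss would be informative and would fall on a primary objective.

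**What to change.** In section 6.3, replace withdrawal from the study with permanent discontinuation of sulfasalazine and return to standard care, with the woman remaining in study follow-up. In section 5.6, apply the same to every stop made by the team, serious or not. State that AE recording continues to the postnatal close-out, that delivery data and the neonatal record review are completed, and that all these data are used, unless she withdraws consent.

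The safety action of stopping the drug is unchanged. The cost is wording in two sections, submitted as a protocol amendment. The close-out contact and neonatal record review are already planned for every participant, so no visits or samples are added.

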**TABLE 1: Example study dose regime:**

|                                                     | Post-breakfast                  | Post-dinner                     | Total daily dose               |
|-----------------------------------------------------|---------------------------------|---------------------------------|--------------------------------|
| Routine study sulfasalazine regime           | 1.5 gram
(3 x 500mg tablets) | 1.5 gram
(3 x 500mg tablets) | 3 grams
(6 x 500mg tablets) |
| Altered sulfasalazine regime if side effects | 1 gram
(2 x 500mg tablets)   | 1 gram
(2 x 500mg tablets)   | 2 grams
(4 x 500mg tablets) |

#### 6.4 MEDICATION PRESCRIPTION AND PARTICIPANT COMPLIANCE

All participants will begin the study as admitted inpatients, with sulfasalazine ordered as regular doses (1.5 grams oral sulfasalazine, twice daily, after food) on their hospital medication chart. The prescribing doctor should denote '*PE sulfasalazine trial*' as the indication on the medication chart, and tick the '*Slow Release*' box.

The timing or refusal of sulfasalazine doses will be documented on the participant's medication chart by the treating midwife or other clinician, as per the hospital's local SOP for medication administration and documentation. A member of the research team will review the patient's medication chart to assess for compliance or deviations from the study protocol of sulfasalazine at each study-related visit.

Any unused sulfasalazine from the supply dispensed for a particular participant will be returned to the local hospital pharmacy at the conclusion of the patient's study participation (as outlined in *Section 6.1.6*).

In the case of a participant who is discharged home prior to delivery, the researchers will rely on verbal reports and medication diary entries of medication regime compliance, confirmed with pill counts of remaining tablets at each outpatient visit attended by the participant.

#### 6.5 OVERDOSE

According to the Manufacturer's information (*Appendix 1*), sulfasalazine has a low per oral toxicity, except in the case of a hypersensitivity reaction. Similar to other sulphonamide drugs, the common signs and symptoms of a hypersensitivity reaction to sulfasalazine include gastrointestinal symptoms (nausea, vomiting and diarrhoea), haematuria, crystaluria or anuria. Central nervous system symptoms such as dizziness or convulsions may occur in more advanced cases, although it is not anticipated that participants will be on a high enough dose of sulfasalazine for long enough for these advanced symptoms to develop in relation to the medication (see *Appendix 1*). There is no specific

antidote for sulfasalazine overdose – any reactions should be treated symptomatically and supportively. Withdrawal of a participant from the trial following a sensitivity reaction will be considered and discussed between the research team, the participant and the participant's treating obstetric unit, and will depend on the nature and severity of the reaction. The *Victorian Poisons Information Centre* can be contacted any time on [name] for advice in the event of a suspected overdose.

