### 1.3 POTENTIAL RISKS TO PARTICIPANTS

We expect the proposed treatment will be safe and well tolerated. Sulfasalazine is classified as a 'category A' drug in pregnancy - it has historically been taken by large numbers of pregnant and child-bearing-aged women; and is not known to cause any increase in the frequency of direct harm, indirect harm, or anomalies in the developing fetus in either humans or animals (13). Importantly,

sulfasalazine therapy is currently continued as a treatment option for pregnant women who have concomitant rheumatoid arthritis or inflammatory bowel disease.

Possible fetal risks:

Not known to cause anomalies in/harm to the developing fetus (13).

Possible maternal risks:

Patients with preterm preeclampsia may experience discomforts or inconveniences relating to their admission to hospital, clinical examinations and blood tests, regardless of whether or not they decide to participate in the study. However, patients recruited to the study would undergo additional examinations and pathology tests that are supplementary to their routine clinical care, and as such, may experience an increase in these discomforts and inconveniences. These additional study requirements will be outlined in detail to all potential participants during the informed consent process.

Sulfasalazine is generally well-tolerated. Side effects relating to the medication can be either dose-related or idiosyncratic.

Dose-related side effects include gastrointestinal side effects (nausea, vomiting and diarrhoea), central nervous system (headache) and hematologic toxicities (including leukopenia, haemolytic anaemia and megaloblastic anaemia). Dose-related symptoms are generally experienced when taking sulfasalazine in larger doses (>4 grams per day) than we propose to administer in this study. Our participants will receive a maximum daily dose of 3 grams of sulfasalazine and will be monitored for dose-related side effects every 1-3 days by a member of the research team.

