#### **7.1 SAFETY ASSESSMENTS**

- Trial participants will have baseline observations performed prior to the administration of the 1st dose of sulfasalazine, and will have their wellbeing reassessed by a study Investigator within 3 hours of taking the 1st dose.
- Trial participants will be monitored for serum levels of sulfasalazine as part of the pharmacokinetic component of the trial. These levels are thought to be directly related to incidences of sulfasalazine-induced hypersensitivity reactions and toxicity (see *Section 6.5* and *Appendix 1*).

- As a part of the routine management for women with preterm preeclampsia, participants will undergo frequent, multimodal monitoring of their own condition, as well as that of their baby. This management and these results will be overseen by the participants' treating clinicians, with additional reviews performed by the research team during the collation of results into the CRF.
- All participants will be public hospital inpatients for at least the initial phase of their study involvement, with 24 hour midwifery, obstetric and critical care staff available in case of a serious medical event
- Following delivery of their baby and the cessation of the sulfasalazine therapy, each participant will undergo routine monitoring and follow-up of their preeclampsia to ensure its timely resolution

Following any AE involving a participant, an obstetrician who is also a member of the research team will review the patient and the history of the AE to establish severity and causality of the event (see *Section 10*), determining whether or not the event was likely attributed to sulfasalazine. They will also arrange for any necessary follow up with the patient in an attempt to ensure that the AE is resolved satisfactorily.

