## OVERDOSAGE

The drug has low acute per oral toxicity in the absence of hypersensitivity. There is evidence that the incidence and severity of toxicity following overdosage are directly related to the total serum sulfapyridine concentration.

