### Signs and Symptoms

Similar to those of any sulphonamides. The most likely symptoms would be gastrointestinal disturbances (nausea, vomiting and abdominal pain), haematuria, crystalluria or anuria. In more advanced cases, central nervous system symptoms such as drowsiness, convulsions, etc., may be observed. Patients with impaired renal function are at increased risk of serious toxicity. There are no documented reports of deaths due to ingestion of large single doses of sulfasalazine.

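### Section 6.5 presents the manufacturer's overdose signs as signs of hypersensitivity, and no section of the protocol body requires sulfasalazine to be stopped for a non-severe rash or mucosal lesion

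*Protocol*

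**What the plan says.** Section 6.5 is headed as the overdose section and cites Appendix 1. It notes that oral toxicity is low except where there is hypersensitivity, then says that "the common signs and symptoms of a hypersensitivity reaction to sulfasalazine include gastrointestinal symptoms (nausea, vomiting and diarrhoea), haematuria, crystaluria or anuria". It adds dizziness or convulsions for more advanced cases. On action it says that "Withdrawal of a participant from the trial following a sensitivity reaction will be considered and discussed between the research team", the participant and her obstetric unit, and that the decision "will depend on the nature and severity of the reaction".

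The source reads differently. Under Overdosage, Appendix 1 says "The drug has low acute per oral toxicity in the absence of hypersensitivity". Its next subsection describes overdosage: "The most likely symptoms would be gastrointestinal disturbances (nausea, vomiting and abdominal pain), haematuria, crystalluria or anuria". Drowsiness and convulsions follow as advanced signs.

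Section 7.1 plans serum sulfasalazine monitoring, says "These levels are thought to be directly related to incidences of sulfasalazine-induced hypersensitivity reactions and toxicity", and refers the reader to Section 6.5 and Appendix 1. The only mandatory withdrawal rule for side effects is in Section 6.3: "Any participants who experience severe side effects associated with sulfasalazine therapy will be withdrawn from the study".

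**The concern.** Two faults sit in the same paragraph. First, a caveat about hypersensitivity has been merged with the overdose list that follows it, so the protocol credits the manufacturer with something the manufacturer does not say. Second, the paragraph that links a sensitivity reaction to any action speaks of leaving the trial and does not mention the drug.

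Someone using Section 6.5 to recognise a reaction would look for gastrointestinal, urinary and central nervous system signs rather than rash, fever or mucosal lesions. On finding a mild rash, they would read of a discussion where the product information says to stop. Appendix 1 places most serious skin reactions in the first month of treatment. Section 1.3 expects a few weeks of dosing at most, so treatment falls largely within that window. Maternal safety is part of the primary objective (Section 2.1.1).

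**Working it through.** No arithmetic beyond counting applies. The documents give no rate of hypersensitivity, so I do not estimate how many of the 20 women might be affected.

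**Step 1: where the eight signs in Section 6.5 come from.** The hypersensitivity column covers four parts of Appendix 1: Hypersensitivity, DRESS and Serious Skin Reactions (all under Precautions), and Hypersensitivity Reactions (under Adverse Effects).

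| Sign in Section 6.5 | Appendix 1 overdosage list | Appendix 1 hypersensitivity text | Dose-related in Section 1.3 |
|---|---|---|---|
| Nausea | yes | no | yes |
| Vomiting | yes | no | yes |
| Diarrhoea | no | no | yes |
| Haematuria | yes | no | no |
| Crystalluria | yes | no | no |
| Anuria | yes | no | no |
| Dizziness | no | no | no |
| Convulsions | yes | no | no |
| **Total** | **6 of 8** | **0 of 8** | **3 of 8** |

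The two signs that do not match the overdosage list are substitutions: diarrhoea for abdominal pain, and dizziness for drowsiness.

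**Step 2: the reverse comparison.** Appendix 1 names these for hypersensitivity:
- skin rash and mucosal lesions (Serious Skin Reactions);
- fever and lymphadenopathy, possibly before any rash (DRESS);
- anaphylaxis, periorbital or facial oedema, conjunctival and scleral injection, and nephrotic syndrome (Hypersensitivity Reactions);
- organ involvement, including hepatitis, nephritis, myocarditis, pneumonitis and blood abnormalities (Hypersensitivity).

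Section 6.5 names none of them. Section 1.3 names rash, hepatitis and pneumonitis, with agranulocytosis and aplastic anaemia, as idiosyncratic effects to be monitored. Mucosal lesions, fever, lymphadenopathy, facial oedema and anaphylaxis do not appear in Sections 1 to 15.

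**Step 3: what happens to a woman with a non-severe rash.**
- Section 6.3 mandates withdrawal only for severe effects. Section 10.4.4 defines severe as keeping a woman from her usual daily activities, which a first rash need not do. The dose reduction in Section 6.3 is for gastrointestinal effects only.
- Section 6.5 prompts a discussion of trial withdrawal and does not mention stopping the drug.
- Section 5.6 lets the team discontinue the drug, at its discretion.
- Section 14.6 ends dosing at delivery or withdrawal.
- Appendix 1, Serious Skin Reactions, says to stop when a rash, mucosal lesion or other hypersensitivity sign first shows.

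Only the last of these requires a stop, and it is in the attachment, not the protocol body.

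**The case against.** The best defence is that this is a transcription slip in a paragraph whose context plainly signals overdose, and that its consequences are already covered. Much of that stands:
- Section 1.3 names rash, hepatitis and pneumonitis and commits to monitoring.
- Section 4.3 excludes women with contraindications, which in Appendix 1 include known hypersensitivity to sulfasalazine, sulfonamides or salicylates.
- Section 7 has a check 30 to 180 minutes after the first dose. Section 7.1 has an obstetrician on the research team review the woman after any adverse event. Section 10.2 records doubtful events as adverse events.
- Section 7.1 points to Appendix 1 as well as to Section 6.5, so the correct signs are within reach.
- Appendix 1, under Potential Toxicity, ties the immediate stop to serious reactions and allows rashes to be controlled with antihistamines or, if needed, corticosteroids. That sentence concerns symptom control and does not cancel the stop instruction under Serious Skin Reactions.

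A reader might infer that the protocol tells investigators to keep dosing through a hypersensitivity reaction. It does not. Section 6.5 concerns withdrawal from the trial, and Section 5.6 separates leaving the study from stopping the drug. The fault is silence, not a contrary instruction.

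A reader might also infer a sharp conflict with Section 6.3 over gastrointestinal symptoms. The tension is mild: Section 6.5 lets the response vary with the reaction, and Section 6.3 is the specific rule for those symptoms.

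**Conclusion.** The point holds. Section 6.5 misreports its cited source on the signs of hypersensitivity, and the protocol body has no rule to stop sulfasalazine for a non-severe rash or mucosal lesion. It is wrong as written, low to moderate in severity, and should be corrected. The safeguards above limit the practical risk but do not correct the list or supply the missing stop rule.

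The finding rests on the text alone. It does not show that any investigator would miss a reaction, and it affects no endpoint, sample size or analysis.

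It would be going too far to conclude that every sign in the manufacturer's hypersensitivity text should trigger an automatic stop. Hepatic, renal and blood findings can be the disease under study, and I take it as a clinical assumption that facial oedema can be too. A blanket rule could stop treatment because of preeclampsia itself.

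**What to change.** Amend Section 6.5 as follows:

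1. Label the existing list as signs of overdose.
2. List the hypersensitivity signs separately, taken from the four parts of Appendix 1 in Step 2.
3. Stop sulfasalazine at the first skin rash, mucosal lesion or anaphylaxis, and immediately for any serious hypersensitivity reaction. For fever or lymphadenopathy, evaluate at once and stop if no other cause is established.
4. Send signs that overlap with preeclampsia or HELLP to prompt investigator causality review under Sections 7.1 and 10.4.2, without an automatic stop. These are facial oedema without other allergic features, and hepatic, renal, haematological or nephrotic findings.
5. Leave mild to moderate gastrointestinal symptoms to Section 6.3.

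Word items 3 and 4 in terms of stopping the drug, not leaving the trial. Follow-up can then continue, in line with Section 8, which plans data collection regardless of compliance where possible.

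The cost is a few sentences and the approvals that Section 14.1 requires for an amendment. A few women may stop treatment for an unrelated rash. The causality review adds little, since Section 7.1 already requires obstetrician review after any adverse event.
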